#### Sample size

As this is a pilot study, which has the primary goal of evaluating the feasibility of the interventions and not ensuring there is adequate power to detect between-group differences, a formal sample size calculation is not required [48]. However, the researchers recognise that the sample size will need to be large enough to provide a degree of accuracy around the estimated effect of the interventions on a desired outcome (i.e. between-group difference in CRF which would be the primary outcome in an RCT) which would indicate whether a definitive RCT is worth pursuing. We estimated that we would need to recruit approximately 10% of the number of participants needed for a full-scale RCT. Based on previous research in this area [67], a sample size calculation for a definitive RCT indicates that we would need to recruit 484 participants. Therefore, allowing for 20% attrition, we aim to recruit 60 participants for this pilot study to inform the power analysis for a full-scale RCT.

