#### Statistical methods

To evaluate the feasibility of the intervention, the number of eligible participants recruited, randomised and retained as well as dropouts lost to follow-up will be analysed as percentages. Data on participants attendance adherence to and compliance with prescribed interventions (i.e. average adherence to reps, sets, HR) will be analysed and the mean results reported as percentages. The incidence of adverse events (an adverse event defined as an event which a participant identifies a problem caused by the exercise programme that required the participant to seek treatment from a health professional and/or prevents participation in the programme) will also be analysed as percentages across all interventions. The acceptability of trial procedures based on participants’ experiences will be explored qualitatively as outlined in this protocol below. Feasibility data will be used to inform the development of a potential full-scale RCT.

In line with CONSORT guidance, the analysis of secondary outcomes will be conducted on an intention to treat basis. All data collected from participants (sociodemographic information, outcome questionnaire scores etc.) will be coded, cleaned and checked for errors. The data will then be entered into the Statistical Package for the Social Sciences (SPSS Version 26) for analysis. The study’s statistician ([name]) will remain blinded to group allocation until the analysis is complete. The change in mean values before and after intervention will be calculated for secondary outcomes. Analysis of variance (ANOVA) and *t*-tests will be applied to compare between-group and within group-differences at baseline and follow-up for each outcome. If there are sufficient participants (*n* = 60), the data will be analysed using analysis of covariance (ANCOVA) with the age and BMI as covariates. Statistical significance will be defined as *p* ≤ 0.05.

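### The secondary analysis is labelled intention-to-treat, but no named method includes a woman without a 12-week value or adjusts for the outcome's own baseline

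*Protocol article*

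**What the plan says.** Under Statistical methods, the protocol article says that "the analysis of secondary outcomes will be conducted on an intention to treat basis". The same paragraph gives the summary measure, "The change in mean values before and after intervention will be calculated for secondary outcomes", and says that ANOVA and t-tests "will be applied to compare between-group and within group-differences at baseline and follow-up for each outcome". One further model is offered if there are enough participants (n = 60): "the data will be analysed using analysis of covariance (ANCOVA) with the age and BMI as covariates". The Abstract words that condition in terms of participants recruited.

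Follow-up assessment provides one post-baseline visit, within seven days of the end of the 12-week period, and all participants are to be approached for it. Sample size says "allowing for 20% attrition, we aim to recruit 60 participants for this pilot study". It derives that target from "approximately 10% of the number of participants needed for a full-scale RCT", where "a sample size calculation for a definitive RCT indicates that we would need to recruit 484 participants". The same section says the pilot should give some accuracy around the between-group fitness difference and inform the power analysis of the full trial.

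Losses to follow-up appear under Statistical methods only as a feasibility percentage.

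**The concern.** The label and the methods do not meet. A change score needs two values, and a follow-up comparison needs a follow-up value. A woman without the 12-week visit has neither, and no named step supplies one. Read as written, the 12-week comparisons cover the women who were measured, while the label may lead a reader to think that all randomised women are included.

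The methods also leave out the covariate that would help most. The ANCOVA lists age and BMI but not the baseline value of the outcome. Except where BMI is itself the outcome, drop-out that depends on baseline fitness or strength is therefore not directly adjusted for. Such drop-out could plausibly differ by arm: the exercise arms attend three supervised sessions a week, while the control arm is asked to change nothing and is offered a programme afterwards.

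At stake is the between-arm fitness estimate, which is a secondary outcome here but is the planned primary outcome of the definitive trial.

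**Working it through.** **Inputs.** From the article: 484 women for the definitive trial, a 10% pilot fraction, 20% attrition, a target of 60 (Sample size); allocation 1:1:1:1 (Trial design); one follow-up visit (Follow-up assessment). Assumed, because the article gives no figure: the SD (set to 1), attrition by arm, the gap between leavers and completers, and the correlations used in steps 4 and 5.

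**1. The plan's own target.** 0.10 × 484 = 48.4, and 48.4 / (1 − 0.20) = 60.5; rounding 48.4 to 48 first gives exactly 60. The target reproduces. It also shows that the sizing counts on about 48 women with usable data, since inflating for attrition is needed only if attrition means lost outcome data.

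**2. Women in the 12-week comparison.** 60 × 0.80 = 48, or 12 per arm instead of 15. As a check, an ANOVA on change was fitted to 60 simulated records with 12 follow-up values missing; it used 48.

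**3. Bias in an arm difference, general form.** If a fraction d of an arm leaves, and leavers' mean change differs from completers' by D, the completers' mean is off by d × D. With the same D in both arms, the difference between arms is off by (d₁ − d₂) × D.

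| Attrition, arm 1 vs arm 2 | D = 0.25 SD | D = 0.5 SD | D = 1.0 SD |
|---|---|---|---|
| 20% vs 20% | 0 | 0 | 0 |
| 30% vs 10% | 0.05 | 0.10 | 0.20 |

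**4. Baseline-driven drop-out, an extreme case.** Suppose exactly the lowest 20% on baseline leave one arm and nobody leaves the other. The baseline mean of those remaining rises by φ(−0.842)/0.8 = 0.350 SD. With an absolute correlation of 0.3 to 0.5 between baseline and change, the arm's mean change shifts by 0.3 × 0.350 = 0.105 to 0.5 × 0.350 = 0.175 SD. Adjusting for baseline removes this shift, if the model is right, because drop-out then depends only on an observed value.

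**5. Precision.** Let r be the correlation between baseline and follow-up, with equal variances at both visits. The error variance is 2(1 − r) for a change score and 1 − r² for a baseline-adjusted analysis. The ratio is 2/(1 + r): 1.33 at r = 0.5 and 1.11 at r = 0.8.

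**6. Scale.** The 95% CI half-width for a two-arm difference is t × √(2/n): 0.75 SD with 15 per arm and 0.85 SD with 12. The biases above are smaller than this sampling uncertainty, but they do not average out.

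**7. The n = 60 condition.** An ANCOVA with four arms plus baseline, age and BMI has 1 + 3 + 3 = 7 parameters. With 48 women, 48 − 7 = 41 residual degrees of freedom remain. The adjusted model does not need 60 women.

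**The case against.** **The article is silent; it does not exclude anyone.** A reader might infer that the plan drops every woman without a 12-week visit. No sentence says so. Handling of missing values is commonly left to a full protocol or analysis plan, neither of which is shown, and ANOVA or ANCOVA could be run on imputed data. This stands, so the absence of an imputation rule is not the point here. The point is the methods that are stated.

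**Intention-to-treat can mean analysis by assigned arm among those observed.** The named tests satisfy that meaning, and approaching all participants for follow-up fits it. This also stands: label and methods are unmatched rather than contradictory, and the article should say which meaning it intends.

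**A reader might infer that attrition rules out the ANCOVA.** It does not. The Abstract ties the condition to recruitment, so 60 recruited women satisfy it even if 48 are measured. What remains is that a recruitment count is a poor reason to adjust or not.

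**The 20% is a sizing allowance, not a forecast.** Agreed. Women who stop exercising may still attend, and 48 is what the allowance implies.

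**The bias figures are chosen.** Agreed. A reader might take a shift of 0.35 SD, the result if the worst 20% of responders left one arm only, as the expected error. Nothing in the article supports that pattern, and the change proposed here would not repair it.

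**A mixed model gains little with one follow-up visit.** Largely true: a woman without that visit contributes only her baseline, so the result is close to a baseline-adjusted ANCOVA in completers. Either model is therefore acceptable. The gain comes from using the baseline value.

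**Conclusion.** The point holds in limited form. The stated methods neither include a woman without a 12-week value nor adjust for the outcome's baseline, so the intention-to-treat label is not matched by the analysis as written. At the 20% allowance, about 48 of 60 women would contribute at 12 weeks.

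Bias in the arm differences is possible, not demonstrated. It requires drop-out related to the outcome together with a difference between arms in who leaves or how many. The 0.05 to 0.20 SD and 0.105 to 0.175 SD ranges hold only under the assumptions shown, and like attrition with like leavers gives zero. The precision loss from unadjusted change scores does not depend on drop-out: 11% to 33% more variance for r between 0.8 and 0.5.

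The consequence is confined to secondary outcomes of a pilot whose main outcome is feasibility. It is still worth correcting before analysis, because the fitness estimate is meant to inform the definitive trial and the better analysis uses data already being collected.

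**What to change.** In Statistical methods:

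- For each secondary outcome, make the main between-arm analysis a model that uses the baseline value of that outcome. Either of two will do: a likelihood-based constrained longitudinal model (baseline and 12-week values of all randomised women, common baseline mean, arm effects at 12 weeks), or an ANCOVA by assigned arm with the outcome's baseline as covariate.
- Keep age and baseline BMI as further covariates, but omit BMI as a covariate when BMI is the outcome.
- Remove the n = 60 condition.
- Report arm differences with 95% CIs.
- State what intention-to-treat means for a woman with no 12-week value. Describe any analysis limited to women with both visits, including the ANCOVA if no values are imputed, as complete-case by assigned arm.

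The cost is wording only: no extra data or visits are needed, and the model can be fitted in the named software. The limitation is that the model assumes data are missing at random given observed values. With a single follow-up visit it cannot correct drop-out driven by unobserved response, and the report should say so.

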### Hypotheses tested

Primary null hypothesis: Post intervention, there is no difference in outcomes (CRF, strength, body composition, self-reported) between participants randomised to the exercise interventions and the control.

Secondary null hypothesis: Post intervention, there is no difference in outcomes (CRF, strength, body composition) between participants randomised to the aerobic exercise, resistance training and combined training groups.

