## Discussion

We have presented the rationale and design of a pilot randomised controlled trial which will investigate and evaluate the effectiveness of different training modalities (aerobic, resistance and combined) in women living with obesity compared to a non-exercise control. The results of this study will help inform exercise prescription for women living with obesity and will be presented as soon as they are available.

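### Within-arm and baseline significance tests are planned for every outcome, no test is tied to the stated hypotheses, and the conditional ANCOVA omits the outcome's baseline value

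*Protocol article*

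**What the plan says.** All places are in the protocol article.

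- **Hypotheses tested.** The primary null is that "there is no difference in outcomes (CRF, strength, body composition, self-reported) between participants randomised to the exercise interventions and the control". The secondary null concerns differences "between participants randomised to the aerobic exercise, resistance training and combined training groups".
- **Aims and objectives.** The secondary objective is the mean difference between the four groups at 12 weeks.
- **Statistical methods.** Pre-post change is calculated for the secondary outcomes, and ANOVA and t-tests "will be applied to compare between-group and within group-differences at baseline and follow-up for each outcome". "Statistical significance will be defined as *p* ≤ 0.05". No test or contrast is assigned to either null. ANCOVA with age and BMI as covariates is conditional on n = 60.
- **Abstract.** It repeats that ANOVA and t-tests will evaluate within-group as well as between-group differences, and makes ANCOVA conditional on enough participants being recruited.
- **Sample size.** The goal is feasibility, "not ensuring there is adequate power to detect between-group differences". Sixty women are to be recruited, allowing for 20% attrition.
- **Discussion.** "The results of this study will help inform exercise prescription for women living with obesity".

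**The concern.** Both hypotheses and the secondary objective ask about differences between randomised arms. The plan nevertheless commits to significance tests that answer other questions.

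A within-arm pre-post test sets the control arm aside. It credits the programme with everything that changes between two visits: familiarity with the test, regression to the mean and time trends. The strength measures show the risk, because Muscular strength has inactive women instructed in bench-press form at the baseline 5RM test and the same test is repeated 12 weeks later. A between-arm test at baseline examines a null that randomisation already makes true.

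With small arms, separate within-arm p-values can easily show one mode as significant and another not when the two do equally well. The Discussion's statement about exercise prescription makes that pattern easy to over-read. The between-arm comparison that the hypotheses do ask for is left without a named contrast, and nothing adjusts it for the outcome's starting value.

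**Working it through.** **Arm size.** The plan's own figure reproduces: 0.10 × 484 = 48.4, and 48 / (1 − 0.20) = 60 (48.4 / 0.80 = 60.5, which rounds up to 61). The inputs behind 484 are not given, so that figure cannot be checked. With 1:1:1:1 allocation, 60 / 4 = 15 per arm randomised. After 20% attrition, 60 × 0.80 = 48, or 12 per arm.

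**Within-arm tests.** The documents give no effect size, so the standardised change dz (mean change divided by the SD of change) is an assumption and is shown as a range. The test is a two-sided paired t-test at 0.05. Its power p comes from the noncentral t distribution with n − 1 df and noncentrality dz × √n. If the three exercise arms share the same dz, the chance that they do not all agree on significance is 1 − p³ − (1 − p)³.

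| dz | n = 12: power | n = 12: disagree | n = 15: power | n = 15: disagree |
|---|---|---|---|---|
| 0.2 | 0.097 | 26% | 0.112 | 30% |
| 0.3 | 0.158 | 40% | 0.192 | 47% |
| 0.5 | 0.353 | 69% | 0.438 | 74% |
| 0.6 | 0.475 | 75% | 0.580 | 73% |
| 0.7 | 0.599 | 72% | 0.713 | 61% |
| 0.8 | 0.714 | 61% | 0.821 | 44% |
| 1.0 | 0.883 | 31% | 0.949 | 15% |

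Example at n = 12, dz = 0.6: 1 − 0.475³ − 0.525³ = 1 − 0.107 − 0.145 = 0.748. The formula peaks at 0.75 when p = 0.5, so 75% is the ceiling and not a typical value.

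**Against control.** If all four arms, control included, share the same dz, the chance that at least one exercise arm is significant while control is not is (1 − (1 − p)³)(1 − p). For dz of 0.3 to 0.8 this is 28% to 47% at n = 12 and 18% to 46% at n = 15.

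**Baseline tests.** Any baseline difference between randomised arms is due to chance, so each test rejects about 5% of the time by construction. Table 2 without height, with activity and sedentary time counted separately and one score per questionnaire, gives 7 + 1 + 3 + 6 = 17 variables. One omnibus test on each would give on average 17 × 0.05 = 0.85 significant imbalances that carry no information.

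**Adjustment.** Let r be the correlation between an outcome's baseline and 12-week values, with equal variances. Relative to comparing follow-up values alone (variance 1), comparing change has variance 2(1 − r), and adjusting for baseline has variance 1 − r². Since 2(1 − r) − (1 − r²) = (1 − r)² ≥ 0 and 1 − r² ≤ 1, baseline adjustment is, apart from the small cost of estimating the slope, never less precise than either. The planned covariates supply this only where BMI is itself the outcome and baseline BMI is meant.

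**The n = 60 condition.** If n counts women analysed, the plan's own attrition allowance (48 completers) makes the unadjusted tests the expected analysis. If it counts women recruited, as the Abstract's wording suggests, one woman short of target changes the analysis method. Under either reading the model depends on recruitment or retention.

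**The case against.** A reader might infer that the planned tests cannot assess the primary null. The documents do not support that. Between-group tests at follow-up are planned, and the unspecified t-tests could include exercise versus control. The hypothesis names exercise interventions in the plural and never says that the arms are pooled. The four-group null of equal means is the joint null of the two hypotheses, so an omnibus ANOVA is a coherent first step. The contrast is undefined, not excluded.

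A reader might also infer that a pooled exercise-versus-control contrast would recover lost power. At 12 per arm it has 65% power against 46% for the omnibus test if every mode works by 0.8 SD. If only one mode does, it has 12% against 46%. The Background reports combined training as the most promising, so equal effects cannot be presumed, and the power argument is not used here.

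Nor do the documents support saying that false-positive modality claims will follow, or counting every pairwise test on every outcome. The plan does not say that all six pairwise tests will be run, and nowhere proposes to compare modes through separate within-arm p-values. Multiplicity handling may sit in an analysis plan that is not shown.

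It also stands that efficacy is secondary, power is disclaimed, and the Abstract's discussion gives the purpose as informing future research. This limits the seriousness of the point. It does not make the within-arm and baseline tests useful: these are stated choices, not details left for later.

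**Conclusion.** The point holds as a badly fixed analysis choice for the secondary outcomes of a pilot, and should be corrected. The article plans within-arm and baseline significance tests for each outcome, assigns no test to either stated null, and makes adjustment conditional on n = 60 with covariates that leave out the outcome's baseline value. With identical true change, the three exercise arms would disagree on within-arm significance about 15% to 75% of the time. That range assumes standardised changes of 0.2 to 1.0, 12 to 15 women per arm, independent arms and two-sided tests at 0.05. It describes what can happen and does not predict what will be reported.

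**What to change.** - For each outcome, fit one model of the 12-week value on arm, adjusted for that outcome's baseline value, whatever n is reached. Age and BMI may stay as covariates.
- For the primary null, report each mode minus control, and the average of the three if a pooled comparison is intended. State which is meant.
- For the secondary null, report the three between-mode differences.
- Give all of these as estimates with 95% CIs, labelled exploratory. This also serves the Sample size section's wish for accuracy around the estimated effect.
- Describe baseline values and within-arm change without p-values.
- Limit the Discussion's prescription statement to informing a definitive trial.

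The cost is wording only, with no extra data and fewer tests. The downside is that the report could no longer state that an individual arm improved significantly.

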**Methods and analysis:**

Sixty women (aged 18–50) with obesity (body mass index [BMI] ≥ 30 and/or waist circumference ≥ 88 cm) who are physically inactive, have no unstable health conditions and are safe to exercise will be recruited from September 2021 to December 2022. The main outcome will be feasibility and acceptability of the intervention and procedures. Trial feasibility outcomes will be evaluated to determine if a definitive trial should be undertaken. Trial acceptability will be explored through follow-up qualitative interviews with participants. Secondary outcomes will include CRF (predicted VO_2_ max), anthropometrics (i.e. BMI), strength (5RM bench press, leg dynamometry, grip strength) and other health outcomes (i.e., pain). Participants will be block randomised into one of four trial arms (aerobic exercise, resistance training and combined training groups, non-active control group) and measurements will be completed pre- and post-intervention. The exercise groups will receive an individualised supervised exercise programme for 3× sessions/week for 12 weeks. The change in mean values before and after intervention will be calculated for primary and secondary outcomes. ANOVA and *t*-tests will be applied to evaluate within-group and between-group differences. If sufficient participants are recruited, the data will be analysed using ANCOVA with the age and BMI as covariates.

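### The planned ANCOVA leaves out the baseline value of the outcome, and its use hangs on an ambiguous and unnecessary n = 60 condition

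*Protocol article*

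**What the plan says.** The Statistical methods section of the protocol article sets out the analysis of secondary outcomes in three steps.

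- Pre-post change: "The change in mean values before and after intervention will be calculated for secondary outcomes".
- ANOVA and t-tests: these "will be applied to compare between-group and within group-differences at baseline and follow-up for each outcome". The text does not say whether they are run on the change scores or on the values at each time point.
- A conditional adjusted analysis: "If there are sufficient participants (*n* = 60"), then "the data will be analysed using analysis of covariance (ANCOVA) with the age and BMI as covariates".

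The Abstract words the condition differently and gives no number: "If sufficient participants are recruited, the data will be analysed using ANCOVA with the age and BMI as covariates".

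The Sample size section shows where 60 comes from: "allowing for 20% attrition, we aim to recruit 60 participants for this pilot study". It is therefore the number to be recruited, with losses already allowed for.

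The Baseline assessment and Follow-up assessment sections together mean that fitness, strength, body composition and the questionnaires are all recorded both before and after the 12 weeks.

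**The concern.** Two features of the adjusted analysis are badly fixed.

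First, in a pre-post design the outcome's own baseline value is usually its strongest predictor. It is collected here for every secondary outcome, yet only age and BMI are named as covariates. With 15 women per arm, or about 12 after losses, chance differences between arms at baseline can be sizeable. A comparison of 12-week values alone carries them into the estimate. Change scores remove the baseline difference but over-correct for it when the correlation is below 1, and so lose some precision.

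Second, whether the adjusted model is used at all depends on a sample-size condition that equals the full recruitment target, and the text does not say which women are counted. The choice of model is then settled by how recruitment or retention turns out, and on an unclear rule it could be settled after the data are seen.

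What is at stake is the precision of the secondary effect estimates. The Sample size section wants those estimates, fitness in particular, to be accurate enough to indicate whether a definitive trial is worth pursuing.

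**Working it through.** **1. Reproduce the target of 60.** The Sample size section says that "a sample size calculation for a definitive RCT indicates that we would need to recruit 484 participants", and that "we would need to recruit approximately 10% of the number of participants needed for a full-scale RCT".

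- 10% of 484 = 48.4.
- Allowing for 20% loss: 48.4 / 0.8 = 60.5. Starting from 48: 48 / 0.8 = 60.

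The stated 60 is reproduced, and the number expected with 12-week data is 60 × 0.8 = 48, or 12 per arm at 1:1:1:1.

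**2. Test the n = 60 condition on each reading.**

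- *Recruited.* It is met if recruitment reaches its target exactly or better, even if only 48 women are then analysed. At 59 recruited it fails.
- *Analysed.* It requires no losses at all from 60 recruited, whereas the plan expects 12. At 20% loss, 60 / 0.8 = 75 women would have to be recruited.

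**3. Is a condition needed?** Error degrees of freedom with 48 analysed and four arms:

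| Model | Error df |
|---|---|
| ANOVA | 48 − 4 = 44 |
| ANCOVA, age and BMI | 48 − 4 − 2 = 42 |
| ANCOVA, age, BMI and baseline outcome | 48 − 4 − 3 = 41 |

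Three covariates cost three degrees of freedom out of 44. The adjusted model can be fitted well below 60.

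**4. Chance imbalance at baseline.** The standard error of a two-arm baseline difference, in SD units, is √(2/n): √(2/15) = 0.37 at 15 per arm and √(2/12) = 0.41 at 12 per arm.

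**5. Gain from the baseline covariate.** Let r be the correlation between baseline and 12-week values, with equal variances at both times. The documents give no r, so 0.5 to 0.8 is an assumption. The variance of a between-arm difference, relative to comparing follow-up values alone, is:

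- follow-up only: 1
- change score: 2(1 − r)
- baseline-adjusted ANCOVA: 1 − r²
- ANCOVA against change score: (1 − r²) / [2(1 − r)] = (1 + r)/2

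| r | Change score | ANCOVA | Saving vs follow-up only | Saving vs change score |
|---|---|---|---|---|
| 0.5 | 1.00 | 0.75 | 25% | 25% |
| 0.7 | 0.60 | 0.51 | 49% | 15% |
| 0.8 | 0.40 | 0.36 | 64% | 10% |

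At 12 per arm the standard error of a two-arm difference at r = 0.7 is √(2/12) = 0.41 SD for follow-up only, √(0.60 × 2/12) = 0.32 SD for change, and √(0.51 × 2/12) = 0.29 SD for ANCOVA.

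These savings are against analyses with no covariates. Against the planned age-and-BMI ANCOVA, the same formula applies with r taken as the correlation that remains after age and BMI are accounted for.

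**The case against.** The strongest reply is that the condition probably means recruited women. The Abstract speaks of recruitment, the Sample size section uses 60 as a recruitment target, and the analysis is declared intention to treat. This stands. A reader might infer that the plan's own attrition makes the ANCOVA unattainable and that the trial will therefore fall back on unadjusted tests. The documents do not support that. The fallback follows only if 60 means analysed women, or if recruitment falls short. What remains is that the rule is ambiguous and has no purpose on either reading.

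A second reply is that pre-post change is calculated. If ANOVA is run on it, baseline is already partly used, and at high r the further gain is small: (1 + 0.9)/2 = 0.95, a 5% saving at r = 0.9. That also stands, but the text does not say that change is what the tests compare. Under randomisation neither follow-up-only nor change-score comparison is biased in expectation. The loss is in precision and in exposure to chance imbalance.

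Third, a reader might infer that the definitive trial would be sized on an inflated SD. The documents do not say that its SD will come from this model, and the pilot data allow the SDs and the correlation to be estimated whichever test is reported.

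Finally, whether BMI means baseline BMI is mainly a clarification. If it does, BMI as an outcome is already baseline-adjusted, so the omission then applies to the other outcomes.

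**Conclusion.** The concern holds for the covariate list on any reading of the condition: age and BMI are named, and the outcome's baseline value is not. It holds for the condition in a limited form. The n = 60 rule is ambiguous, leaves no slack if it counts recruits, conflicts with the expected 48 completers if it counts women analysed, and is unnecessary because 48 women leave 41 error degrees of freedom.

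The size of the precision loss depends on an assumed correlation. Over 0.5 to 0.8, variance would fall by 25% to 64% against follow-up-only comparison and by 25% down to 10% against change scores.

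This is a should-fix point, not a fatal one. The primary aim is feasibility and acceptability, analysed as percentages and through interviews, and the ANCOVA plays no part in that. The Sample size section also disclaims power for between-group differences. What improves is the quality of the secondary estimates intended to inform a later trial.

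**What to change.** In the Statistical methods section, and to match in the Abstract:

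1. Delete the n = 60 condition.
2. For each secondary outcome, make the main between-group analysis an ANCOVA of the 12-week value on arm, the baseline value of that outcome, age and baseline BMI. Where BMI is the outcome, enter baseline BMI once.
3. State that the BMI covariate is the baseline measurement.
4. Report adjusted mean differences between arms with 95% confidence intervals from this model.

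The cost is a change of analysis wording. No new data, visits or participants are needed, and it should be made before the data are analysed.
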